### Data collection and management

Data collection will be conducted by the research staff at the study site under the supervision of the Kenyan investigators. A household and fisher survey will be used to gather data on demographics, socioeconomics, hygiene, sanitation, mother and child health, diet, anthropometry, COVID livelihood impacts, household decision making, awareness/knowledge of fish consumption, and fishing characteristics at baseline and endline. Dietary intakes will be measured using a Kenya-specific semi-quantitative food frequency questionnaire (FFQ) (32). The survey will be developed using the Research Electronic Data Capture (REDCap™) platform and collected electronically using password protected tablets. To assure the quality of data entry the survey will utilize REDCap™'s built-in data validation. The team will also be able to track access of data, instruments, and reports through an electronic audit trail. To minimize missing data the field team coordinators will review all REDCap™ records for completeness prior to uploading the data to the secure REDCap™ server hosted by Washington University in St Louis. If any issues are found the coordinators will follow up with the enumerator responsible for the data entry. Fisheries catch, take home amount, and income data will be collected at least four times monthly at landing sites using paper forms that are then entered into Microsoft Excel by the fisheries field team and stored on password protected computers. Excel data entry is mediated with built-in validation to a given list of marine fish species found locally. All paper forms will be stored in a locked filing cabinet when not being processed. Data will be screened for completeness and consistency on a bi-weekly basis, with archival data stored in the password-protected Box cloud storage platform, and if any issues arise, the research team will follow up with the data collectors.

A process evaluation will be used to monitor and ensure consistent administration of the intervention (fidelity of delivery), adoption, and sustainability, three key implementation outcomes (33). The primary focus is on documenting the transition from inputs [nutrition social marketing and fisher support (modified traps)] to the anticipated outputs, outcomes, and impact (Figure 1). Systematically tracking, documenting, and assessing this part of the impact pathway will allow for a more nuanced understanding of the implementation process, how and why the intervention does/does not have the anticipated impact, and facilitate future replication. Mixed methods will be used to collect information along the impact pathways. Table 6 provides an overview of the implementation process outcomes, methods, and data types.

All data collected for this study will be stored on the REDCap™ platform and on Box, a secure, Health Insurance Portability and Accountability Act (HIPAA) and Family Educational Rights and Privacy Act (FERPA) compliant data storage and sharing online platform.

### Study measures

To evaluate intervention impacts, we will assess primary outcomes of child growth along with fish food intakes, and fisheries yield of mature fish. Secondary outcomes of interest, which are also hypothesized to serve as mediating factors between the intervention and primary outcomes, include indicators for child health and diet (dietary diversity, prevalence of diarrhea) and fisheries earnings. Measurement of the targeted nutrition endpoints will occur at two timepoints as part of a household level survey. The household surveys will also collect information on other relevant measures and potentially confounding factors including household expenditures, and household decision-making. Measurement of fisheries focused endpoints will occur at regular intervals over the course of the 12-month intervention at commonly utilized fish landing sites within the study area. Table 5 summarizes measures that correspond with outcomes of interest.

**Table 5 T5:** Study outcomes.

**Construct**	**Methods**	**Indicator**	**Timepoints**

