“We bring our BMU community”	Social marketing + modified traps	Check in on use of modified traps Refresh knowledge of child nutrition Discuss changes they have noticed in the areas where they fish (environment, fish quantity, fish types etc.) Importance of sharing the information they have received with other fishers Activity to develop a persuasive argument to protect the places where they fish and their children's nutrition Commitment to share what they have learned with new fishers and friends

Fisher training, gear modification, and fishing trap distribution constitute the second piece of the intervention. The use of fishing gears modified to decrease juvenile catch has been shown to lead to greater catch diversity and improve the economic value of fishes (16). Second, fishers can gain a competitive advantage when using new gears by fishing new habitats to catch previously targeted species in novel ways (15). This can reduce the impact of fishing on the environment, and in the case of coastal Kenya, coral reefs. Last, gear modifications have been shown to improve harvest efficiency and promote sustainable fish populations by selecting for mature individuals while at the same time improving fisher revenue (29). Using these rationales, our intervention targets fishers using basket traps and provides them with traps modified with escape gaps so immature fish can escape. Trap distribution will occur at landing sites utilized by participating fishers and at local BMU offices. The fishers will also receive training on how to properly maintain the traps they receive. We hypothesize this type of intervention will reduce fishers' dependence on immature fishes, as well as buffer them from potential market variability (30) and enable them to be more resilient to environmental change (31).

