**Primary outcomes**			
Child growth	Anthropometric measures of height and weight	Length-for-age *Z* score (LAZ) Weight-for-age *Z* score (WAZ) Weight-for-length *Z* score (WLZ)	Baseline, 12 mo.
Fish food intakes	24-h intake survey	Fish food intakes in g	Baseline, 12 mo.
Fisheries yield of mature fish	Fish catch survey at landing sites	Monthly catch per unit effort and fish size distribution	5–10 times per month at randomly stratified days over the course of 12 months

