**Secondary outcomes**			
Child diet diversity	24-h intake survey	Diet diversity score	Baseline, 12 mo.
Diarrheal morbidity	HH survey, recall by mother during home visits	Reported acute diarrhea in the last 2 weeks	Baseline, 3, 6, 9, and 12 mo.
Fisheries earnings	Fish catch survey at landing sites	Earnings [in Kenyan shillings (Ksh)] per fishing trip	5–10 times per month at randomly stratified days over the course of 12 mo.

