##### Fisher revenue

During fisheries yield data collection, enumerators will also ask fishers about their operational costs and the revenue generated from selling the fish. Fisher revenue will be represented as Kenyan shillings (Ksh) per fishing trip. These questions will be informed by cultural norms and objects such as food and equipment used as currency when Kenyan shillings cannot be estimated (e.g., bags of rice). Comparisons will be made at the landing site or BMU level to measure the change in earnings pre- and post-intervention as described by Wamukota et al. (35).

A range of other variables will be assessed to control for cofounding factors associated with the cluster design. These variables include but are not limited to child illness (a standard 2-week recall on infectious illnesses including cough, rhinorrhea, fever, and rash), household consumption and assets, and household decision making [Likert scale instrument that captures common domains of decision-making including purchasing decisions; decisions regarding service use (health, education); decisions regarding children's diet, health and education].

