### Analysis

#### Primary and secondary outcomes

Generalized linear regression modeling (GLM), allowing for non-normal distributions, will test the continuous outcomes of HAZ, WAZ, child dietary fish intake, child dietary diversity score, fisheries yield, and fish earnings. As a difference-in-difference analyses, change variables for each outcome will be examined (difference between baseline and endline). For the binomial outcomes of diarrhea morbidity (and other outcomes of stunting and underweight), we will estimate prevalence ratios by the GLM modeling with robust Poisson. If stunting prevalence in this population exceeds the acceptable threshold for use of odds ratios (0.2105), prevalence ratios (PRs) will be used to examine the intervention effect and were considered analogous to relative risk in this longitudinal study. The robust Poisson, with a classic sandwich estimator to correct the inflated variance of standard Poisson, is less affected by outliers.

To test for intervention effectiveness, the two intervention groups will be combined for all hypotheses except the secondary outcome of increased fisher earnings and exploratory hypothesis for differences between social marketing and social marketing + traps intervention groups. Regression models will be adjusted for potential confounding factors including age, sex of the child, corresponding baseline measures, and others found to differ significantly between the trial groups (e.g., maternal education). For fisheries yield, confounding factors will be used to adjust regression models, such as: water temperature, fishing ground area, coral cover, and seasonality. The *P* significance value for Type I error (and one-tailed test) will be *P* < 0.05 and corresponding 95% confidence interval. Diagnostics for regression model assumptions, structure and observations will be applied, and corrective procedures applied as necessary. If selection bias is widely detected with important differences across intervention and control communities, we will apply propensity score analyses (36). Data analyses will be performed with Stata software (version 16.0; StataCorp, College Station, TX) and R (4.1.2).

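### Fisheries yield and earnings are analysed as change from baseline, but their schedule names no pre-trap baseline period, and gear type is not a named covariate

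*Protocol article*

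**What the plan says.** **Schedule.** Study measures states: "Measurement of fisheries focused endpoints will occur at regular intervals over the course of the 12-month intervention". Table 5 gives the timepoints for yield of mature fish as "5–10 times per month at randomly stratified days over the course of 12 months" and for earnings as "5–10 times per month at randomly stratified days over the course of 12 mo". Neither row has a baseline entry. The other four rows (child growth, fish intake, diet diversity, diarrhoea) all have one; the fish intake row, for example, reads "Fish food intakes in g Baseline, 12 mo".

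**Analysis.** The Design section plans longitudinal difference-in-difference analyses for the fisheries outcomes. The Analysis section includes yield and earnings among its continuous outcomes and says that "change variables for each outcome will be examined (difference between baseline and endline"; its models also adjust for the baseline value of each outcome. Under Fisher revenue, comparisons at landing-site or BMU level are meant "to measure the change in earnings pre- and post-intervention".

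**Gear.** According to Interventions, "our intervention targets fishers using basket traps and provides them with traps modified with escape gaps". The eligibility criteria ask only that a household member be a self-employed small-scale fisher. Communities are compared on their mix of gears. The confounders named for the yield model are introduced as examples: "such as: water temperature, fishing ground area, coral cover, and seasonality".

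**The concern.** The study is not randomised. The Design section relies on differencing to deal with residual confounding, and this works only if the first measurement precedes the intervention. The schedule for a primary outcome does not provide for that. The analyst would have to choose, possibly after seeing data, between treating early intervention months as baseline and dropping the differencing. The first choice can subtract part of the trap effect from itself. The second leaves in the estimate any lasting difference between landing sites, and between basket traps and the gears that control fishers use. Hypotheses 7 and 8 (yield and earnings) are both exposed.

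**Working it through.** The article gives no sample size or power figure for catch or earnings, so there is no stated number to reproduce. The total of 400 households rests on height-for-age and is not at issue here.

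**1. Does another passage supply a pre-trap measurement?**
- Data collection and management: the baseline and endline survey covers fishing characteristics; catch and income come from the landing-site forms.
- Fisheries yield of mature fish: yields are compared with their initial level, but that level is not placed before the traps.
- Fisher revenue: a pre-intervention comparison is intended, but no period is scheduled for it.
- Interventions: trap distribution is described by place, not by date.

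The analysis therefore needs a baseline that no passage defines.

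**2. What the change score estimates.** Let g be a constant difference in catch between the trap arm and control (site or gear), and e(t) the trap effect in month t as a share of its full value. Assume a common time trend.
- With a true pre-trap baseline: [g + e(end)] − g = e(end). The constant g cancels.
- With early intervention months as baseline: [g + e(end)] − [g + e(early)] = e(end) − e(early).
- Post-only contrast: g + e(end).

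**3. Share of the full effect recovered** with the first 1 or 3 intervention months as baseline and the last 1 or 3 as endline. The onset patterns are assumptions, because the article gives none.

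| Onset pattern | 1 month | 3 months |
|---|---|---|
| Immediate and constant | 1 − 1 = 0% | 1 − 1 = 0% |
| Linear to month 3, then flat | 1 − 0.333 = 67% | 1 − 0.667 = 33% |
| Linear over 12 months | 1 − 0.083 = 92% | 0.917 − 0.167 = 75% |
| Traps handed out after month 3 | 1 − 0 = 100% | 1 − 0 = 100% |

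**4. Post-only contrast.** Take an assumed gear gap of ±0.30 and an assumed true effect of 0.20, both as shares of mean catch. The estimate is 0.20 + 0.30 = 0.50 or 0.20 − 0.30 = −0.10. With no true effect it is ±0.30. These values only illustrate that the gap passes through in full.

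**5. Which groups are compared?** Table 1 sets hypothesis 7 as social marketing plus traps versus control. The Analysis section combines both intervention groups for every hypothesis except fisher earnings and the exploratory comparison, so yield falls under the combined contrast. In that contrast 100 of 200 intervention households receive no traps. With equal numbers of trips and no effect of social marketing on yield (both assumptions), the trap effect would be averaged down to 100/200 = one half.

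**The case against.** **The authors plainly intend a pre-period.** Fisher revenue speaks of change from before to after, and the models adjust for baseline measures. Early sampling months may precede distribution, Figure 2 is not available in this text, and a condensed article may leave exact dates to the full protocol. This stands as far as it goes: a reader might infer that no pre-trap catch data will exist, and the text does not show that. It does not remove the conflict, because the article states a schedule for these outcomes and that schedule omits the baseline its own analysis uses.

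**Gear is not ignored.** Communities are compared on gear mix, landing-site sampling takes the main gears into account, the covariate list is open, factors that differ between groups may be added, and propensity scores follow if selection bias is found. It would be wrong to say that the gear difference is left uncorrected. But community-level matching does not align individual fishers, the later steps are conditional and do not name gear, and none of them creates a missing pre-period.

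**The size of site differences is unknown.** One could assume a between-site coefficient of variation of 20–30% and compute CV × √(1/k1 + 1/k2). With 4 versus 4 sites, following the roughly four clusters per arm in Sample size, this gives 0.20 × 0.707 = 14% to 0.30 × 0.707 = 21%. With an assumed 2 versus 2 it gives 20–30%. The CV and the landing-site counts are both assumptions, and the result is a standard error rather than a bias, so the conclusion does not use it.

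**Conclusion.** The point holds as an inconsistency on a primary outcome. Study measures and Table 5 do not provide the baseline that Design, Fisher revenue and Analysis require, and the timing of trap distribution, which decides what a change score means, is not stated. Over the onset patterns tried, the share of the trap effect recovered runs from 0% to 100%. The lower end needs an effect that is immediate and constant, with traps in use from the first month, so a near-zero estimate is the worst case and not a prediction. The 0–100% range and the post-only problem are alternatives: which one applies depends on the analysis chosen. The gear point is narrower. There is no gear criterion for control fishers and gear is not among the named yield covariates; a true pre-trap baseline would remove a constant gear gap, and without one the estimate depends on conditional adjustment.

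**What to change.** 1. Define a catch and earnings period before the first trap distribution and the first fisher workshop, in all arms, using the existing landing-site survey. Workshops matter too, because Table 4 asks fishers without modified traps to aim for more mature fish.
2. Enter that period as baseline in both fisheries rows of Table 5, state the distribution date or window, and bring Study measures into line with Design, Fisher revenue and Analysis.
3. Compare like seasons where possible: a baseline in the month before month 1 falls in the same calendar month as month 12. Otherwise keep the seasonality adjustment.
4. Fit an arm-by-period model to the landing-site data, with gear type as a named covariate. Add a basket-trap-only comparison as a sensitivity analysis if numbers allow. It should not be the main analysis, because the Design section itself reports that trap fishers are scarce.
5. State whether hypothesis 7 compares the trap arm or the combined intervention groups with control, and make Table 1 and Analysis agree.

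**Cost.** A few more weeks of sampling that is already set up, or a short delay in distribution. If early sampling months already precede distribution and workshops, only a written definition is needed. Pre-trap catch that is not recorded cannot be recovered later.

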**Primary outcomes**			
Child growth	Anthropometric measures of height and weight	Length-for-age *Z* score (LAZ) Weight-for-age *Z* score (WAZ) Weight-for-length *Z* score (WLZ)	Baseline, 12 mo.
Fish food intakes	24-h intake survey	Fish food intakes in g	Baseline, 12 mo.
Fisheries yield of mature fish	Fish catch survey at landing sites	Monthly catch per unit effort and fish size distribution	5–10 times per month at randomly stratified days over the course of 12 months
**Secondary outcomes**			
Child diet diversity	24-h intake survey	Diet diversity score	Baseline, 12 mo.
Diarrheal morbidity	HH survey, recall by mother during home visits	Reported acute diarrhea in the last 2 weeks	Baseline, 3, 6, 9, and 12 mo.
Fisheries earnings	Fish catch survey at landing sites	Earnings [in Kenyan shillings (Ksh)] per fishing trip	5–10 times per month at randomly stratified days over the course of 12 mo.

#### Primary outcomes

##### Child growth

Anthropometric measures (length/height, weight) will be collected from children and mothers/caregivers at baseline and endline. The Seca Model 874 (Digital) 440 lbs. × 0.1-lb. resolution and the ShorrBoard^®^ stadiometer will be used to collect weight and length measures, respectively. Measures will be converted to weight-for-age *Z* (WAZ), length-for-age *Z* (LAZ)/HAZ, weight. HAZ and WAZ will be generated using World Health Organization (WHO) (34). The Stata Macro available from WHO will be run to derive the indicators using data on child age in months, sex of the child, and child height/weight. Outliers above HAZ/WAZ > 6 or HAZ/WAZ <−6 will be removed.

##### Dietary assessment/fish food intakes

Dietary intakes will be measured using a Kenya-specific semi-quantitative food frequency questionnaire (FFQ) (32). A comprehensive list of foods consumed in Kenya, and specifically along the coast, will be compiled along with ingredients in common dishes. This will be integrated into the survey as an FFQ for 24-h intakes of women of reproductive age, youth, and children ages 6–60 months. Particular attention will be given to fish foods and other animal source foods which will be asked as 24 h and 7-day recalls. Findings from the FFQ will later be converted to the Feed the Future (FTF) indicators of minimum dietary diversity for women and young children. Finally, infant and young child feeding practices (IYCF) practices will be assessed in accordance with the FTF minimum acceptable diet indicator.

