## Methods and analysis

### Design

We aim to test the effectiveness of the multi-component *Samaki Salama* intervention as it intersects with nutrition security and fisheries sustainability in Kilifi County, Kenya. Table 1 details the specific aims and hypotheses.

**Table 1 T1:** Study aims and hypotheses.

**Study aims**	**Hypotheses**
1. Determine the effects of a multi-component social marketing campaign to promote fish nutrition, dietary diversity, and food safety on child growth	**Primary** Hypothesis 1: Children in combined intervention groups have increased height-for-age *Z* by 0.2 compared to children in the control Hypothesis 2: Children in combined intervention groups have increased weight-for-age *Z* by 0.10 compared to children in the control Hypothesis 3: Children in combined intervention groups have increased fish food intakes by 100 g compared to children in the control
	**Secondary** Hypothesis 4: Children in combined intervention groups have increased dietary diversity by 1.2 compared to children in the control Hypothesis 5: Children in combined intervention groups have reduced diarrheal morbidity by 5 percentage points compared to children in the control
	**Exploratory** Hypothesis 6: Children in the social marketing + traps intervention group have increased dietary diversity and fish intake compared to children in the social marketing only group
2. Measure the impact of modified fishing traps with escape gaps on catch dynamics and earnings	**Primary** Hypothesis 7: Fishers in the social marketing + traps intervention group have significantly increased fisheries yields of mature fish compared to fishers in the control
	**Secondary** Hypothesis 8: Fishers in the social marketing + traps intervention group will have significantly increased earnings compared to fishers in the control

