### Interventions

The 12-month *Samaki Salama* intervention introduces practices and technologies that build on existing community assets and expressed needs and preferences of small-scale fishers and their households. The first component of the intervention package, nutrition social marketing, is a novel approach to increase nutrition awareness across multiple stakeholders that draws on psychology, marketing, and communications disciplines (25). Distinct from conventional nutrition education interventions that tend to use more didactic approaches and standardized materials, this strategy draws heavily on contextual factors to identify key messages and delivery platforms. Nutrition-focused social marketing campaigns have been shown to promote active engagement of participants throughout the trial, high compliance to the intervention, sustained behavior change, and low losses to follow-up (26). The effectiveness of social marketing increases if targeted messages are repeated and delivered across different platforms (27) and previous studies indicate that 6 months of animal source food nutrition messaging may not be enough to sustain impact (28). Therefore, we propose a 12-month intervention period.

The nutrition social marketing approach will be developed in close collaboration with the social and behavioral change group at USAID Advancing Nutrition. The focus is on promoting four priority behaviors among infants, young children and women of reproductive age in SSF households: (1) caregivers feed fish to young children 6 months to 5 years daily; (2) caregivers feed an age-appropriate diverse diet, including fish, to children 6 months – 5 years daily; (3) caregivers wash hands and the child's hands with soap or ash before feeding; (4) fathers reserve and take home a small portion of fish for child each day. The social marketing plan and audience analysis, including all materials, messaging, and delivery platform relies on formative research conducted in the study area and piloting of materials prior to implementation. As shown in Table 3, messaging centered on the four priority behaviors will be delivered through diverse channels to mothers/caregivers, fathers, and leaders/members of local institutions. The plans to engage these participants groups reflects a multi-level approach to support improved feeding and care behaviors through individual, family, and community level change.

**Table 3 T3:** Social marketing campaign activities and materials.

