**Institutions**		
BMUs orientations	Staff	Banners Posters Stickers
Health worker orientations	Staff, CHVs	Posters Stickers Bags

*Home visits* are a key component of the social marketing campaign and will occur at a three time points (3, 6, and 9 mo.) in both intervention groups. All homes in the intervention groups (*n* = 200) will be visited at each time point. Visits every 3 months will allow the field team enough time to complete one round of visits before starting the next round. Three visits per household is the maximum the field team anticipates being able to complete within the 12-month intervention. During visits, the team's nutrition education specialists will actively engage with the caregiver and child/children to build a positive relationship, understand their individual needs, and foster change. The suite of social marketing materials available to the field team will be the same for all intervention households but we anticipate that the exact information and materials provided will be tailored to meet the needs of the individual household and child/caregiver dyad. The nutrition team will discuss and identify illnesses before introducing age and stage-specific child feeding and hygiene habits (or recommendations) and help caregivers identify next steps and agree on actions geared toward improving feeding and hygiene practices and better health care. The overarching message caregivers will receive is that fish can be a critical source of nutrients for their child and paying special attention to their child's growth and development now has life-long benefits. Discussions, agreements, and actions taken will be documented and tracked by the nutrition team. Local CHVs in both intervention and control communities will be trained to conduct the home visits so caregivers will have a reliable source of information and support even after the project is completed.

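### H3 and H4 rest on unmasked reports of the behaviours the campaign coaches, and the take-home fish already recorded has no corroborating role in the listed outcomes or analysis

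*Protocol article*

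**What the plan says.** Table 1 (Design) makes H3 primary: "Children in combined intervention groups have increased fish food intakes by 100 g compared to children in the control". H4 is secondary: "Children in combined intervention groups have increased dietary diversity by 1.2 compared to children in the control". Table 5 gives the H3 indicator as "Fish food intakes in g", from a 24-hour intake survey at baseline and 12 months. The dietary assessment section adds: "Particular attention will be given to fish foods and other animal source foods which will be asked as 24 h and 7-day recalls". The diversity score (Child diet diversity) counts how many of seven food groups are reported in the same survey. Fish falls within one of them, flesh foods.

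The first priority behaviour under Interventions is that "caregivers feed fish to young children 6 months to 5 years daily"; the second is a diverse diet every day. At 3, 6 and 9 months, in the intervention groups only, home visitors "help caregivers identify next steps and agree on actions geared toward improving feeding and hygiene practices". Table 3 lists project staff and community health volunteers as delivering these visits.

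On measurement, Data collection and management says: "Data collection will be conducted by the research staff at the study site". The same section says: "Fisheries catch, take home amount, and income data will be collected at least four times monthly at landing sites". Take-home amount is not mentioned in the hypotheses (Table 1), the outcomes (Table 5), the process evaluation (Table 6) or the Analysis section.

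**The concern.** The outcome questions ask whether the child was fed what the campaign asked the caregiver to feed. A caregiver who has agreed to feed fish has a reason to report it that a control caregiver largely lacks. The error would favour the intervention, which is also the natural direction of the one-tailed test in the Analysis section.

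At stake is how a primary endpoint is read. If reported intake rises and height-for-age does not, the plan as listed cannot tell misreporting from a real dietary change that did not affect growth.

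**Working it through.** **1. What is coached against what is asked**

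| Coached in intervention households | Asked at endline |
|---|---|
| Fish for the child every day (behaviour 1) | Grams of fish, 24-hour and 7-day recall (H3) |
| Diverse diet every day (behaviour 2) | Number of food groups reported (H4) |
| Fathers bring some of the catch home for the child (behaviour 4) | Take-home amount at landing sites: collected, no listed outcome |

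The article does not say in words that caregivers answer the diet questions or know their group. Both follow from its content: the children are 6–60 months old, and home visits with branded materials cannot be hidden.

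**2. What difference-in-difference does**

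Let *b* be the mean reporting error in each group (I, C) at baseline (0) and endline (1). The estimated contrast is

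true effect + (b_I1 − b_I0) − (b_C1 − b_C0).

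A stable error cancels. An error that begins with the campaign stays in full, less any matching shift in controls. Matching and propensity scores deal with differences that exist beforehand, and do not reach it.

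**3. Shift in the mean**

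The plan gives no figure for reporting error, so the inputs are assumptions: a share *f* of intervention caregivers over-reports one 50 g portion.

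- H3: 0.20 × 50 = 10 g; 0.40 × 50 = 20 g, which is 10–20% of the 100 g target.
- H4: a falsely reported fish serving adds 1 group only if the child had no other flesh food. The mean shift is at most 0.20–0.40 × 1 = 0.2–0.4 points. No single child can gain more than 1 from fish, which is below the 1.2 target. Other groups could also be over-reported, because diversity is promoted too.

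**4. Chance of a positive test with no true effect**

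The test is against zero, not against 100 g. Inputs: 200 households per side less 20% loss (Sample size section) = 160 completers; one-tailed P < 0.05 (Analysis section). Assumptions: SD of the change score; ICC of 0 or 0.05; 40 completers per cluster (160 over about 4 clusters).

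- DE = 1 + (40 − 1) × ICC, so 1 at ICC 0 and 2.95 at ICC 0.05.
- se = SD × √(2/160 × DE), so 0.112 SD and 0.192 SD.
- P(positive) = Φ(shift/se − 1.645).

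Example: f = 0.30, shift = 15 g, SD 60 g, ICC 0: se = 6.71; 15/6.71 − 1.645 = 0.59; P = 0.72.

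| H3, share over-reporting 50 g | ICC 0: SD 40 / 60 / 100 g | ICC 0.05: SD 40 / 60 / 100 g |
|---|---|---|
| 20% | 0.72 / 0.44 / 0.23 | 0.37 / 0.22 / 0.13 |
| 30% | 0.96 / 0.72 / 0.38 | 0.62 / 0.37 / 0.19 |
| 40% | 1.00 / 0.91 / 0.56 | 0.83 / 0.54 / 0.27 |

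| H4, share adding one group | ICC 0: SD 1.0 / 1.3 / 1.6 | ICC 0.05: SD 1.0 / 1.3 / 1.6 |
|---|---|---|
| 20% | 0.56 / 0.39 / 0.30 | 0.27 / 0.20 / 0.16 |
| 30% | 0.85 / 0.66 / 0.51 | 0.47 / 0.33 / 0.25 |
| 40% | 0.97 / 0.87 / 0.72 | 0.67 / 0.48 / 0.37 |

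The nominal value is 0.05 throughout. These are normal approximations and are rough with so few clusters. The stated sample size of 400 rests on height-for-age and does not bear on this point.

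**The case against.** **This is the ordinary limitation of diet recall in an unmasked behaviour-change study.** True, and nothing in the article contradicts itself here. But H3 is a primary outcome, and a partial check is already being collected.

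**Take-home fish is no clean check.** This stands. Bringing fish home is a promoted behaviour, with a commitment letter and a workshop commitment to it. The catch is weighed, but nothing says the take-home part is, so it may be fisher-reported. A child can also eat more because fish was bought or shared differently within the household. A reader might infer that a flat take-home result should overturn a recall gain; the documents do not support that.

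**Role overlap is not stated.** Also true. A reader might infer that home visitors conduct the endline diet interview. The article says only that research staff collect data, and speaks of nutrition education specialists for visits and an enumerator for survey entry. It does not exclude overlap, however, and Table 5 has diarrhoea, a secondary outcome, recalled by mothers during home visits. Rotas may sit in a field manual that is not shown.

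**Controls are not untouched.** They receive project gatherings and materials, and volunteers in control communities are trained to do home visits. This could narrow the difference in reporting, but the scheduled visits with agreed actions go to intervention households. The process evaluation observes practice at those same visits, so it gives no comparison with controls.

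**Data linkage is unproven.** This stands. Catch sampling is described by landing site and selected days, without saying that records are keyed to enrolled households, and fisheries measurement is placed over the 12-month intervention, so a baseline take-home value is not assured. The Fisher revenue section does plan comparisons before and after the intervention, by landing site or BMU, from the same collection.

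**Conclusion.** The point holds as a risk of differential reporting, of unknown size, in H3 and H4 only. The article shows that the reported behaviours are those coached after baseline, that the change-score analysis would carry any resulting shift, and that take-home fish has no role in the listed outcomes or analysis.

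Under the assumptions above, 20–40% over-reporting gives a chance of a positive H3 from 0.13 to 1.00, and of a positive H4 from 0.16 to 0.97, with no true effect. The width reflects how little is known: the documents give no over-reporting rate, portion size, SD or ICC.

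Two stronger readings go too far. A reader might infer that H3 and H4 would succeed through reporting alone; that depends wholly on the assumed values, and 10–20 g is far from 100 g. A reader might also set one falsely reported serving (1 point) against the 1.2 target and call it most of the effect. That compares one child's maximum with a difference in group means; the mean shift is at most 0.2–0.4.

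H1 and H2 are measured anthropometry and are not exposed to this bias. The change is worth making because it is cheap and bears on a primary outcome.

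**What to change.** **(a) Supporting outcome.** Prespecify take-home fish from the landing-site record as a supporting outcome for H3, compared between the same arms. Use enrolled fishers where records can be linked to households, and otherwise compare by landing site or BMU, as the Fisher revenue section already does for earnings. Confirm the linkage, whether a pre-intervention value exists, and whether take-home fish is weighed or reported. State in advance that a recall gain without a take-home gain will be described as reported intake that was not corroborated, not as absence of an increase.

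**(b) Interviewing.** Assign existing staff so that nobody surveys at endline a household they visited or trained. Ask the diet module before the awareness and knowledge questions.

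**Cost.** One further analysis of data already collected, a sentence on interpretation, a rota and a question order, plus the work of linking records if they are not keyed to households. The downside is that take-home fish is a household measure, misses purchases and redistribution within the household, may be self-reported and is itself promoted. It can corroborate H3 but must not veto it.
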